### Specific assessment protocols

Please refer to Text Supplement  *S1* in the Supplementary material online, Material for more detailed protocols and references for specific study-related assessments.

### Integrative data platform

All data collected for TRUST are combined and stored in a secure research infrastructure at the University Medical Center Hamburg-Eppendorf in pseudonymized form. Data protection policies, as well as technical and organizational measures, were reviewed by the responsible data protection officer at University Medical Center Hamburg-Eppendorf. Whenever possible, pseudonymization and transfer are automated or semi-automated, a) to improve quality via reduction of manual transfer-related errors and b) to enhance privacy by limiting the extent of involvement of study personnel.

Manually collected variables and results of study-related non-routine investigations are captured by trained study personnel using REDCap as a central electronic data capture platform.^18^ Other study data that cannot be sensibly recorded in REDCap, such as large tabular sets of laboratory data, imaging data, time-series data, or data from electroanatomical mapping studies, are stored for further analysis in TRUST’s research database as well as an S3-based object store linked to the patient pseudonyms. For feature extraction from and classification of unstructured data and certain clinical texts, TRUST’s research infrastructure employs natural-language-processing techniques, (small) language models, as well as deep learning (ref. Text Supplement  *S2*).

TRUST's data platform also facilitates remote consent for sub-studies and enables the distribution of online questionnaires during follow-up. Remote consent employs two-factor authentication, using a credential known only to the participant and a second factor delivered by mail. The platform integrates third-party tools, such as web services of the fingertip- and wearable-PPG providers using automatic double pseudonymization, data retrieval, and their integration with the study database.

REDCap’s MyCap extension is used during remote follow-up for regular, continuous collection of patient-reported outcome measures and symptoms.^17^ All external partners, external platforms, and communication with participants are handled via specific unique identifiers, different from the main pseudonyms. This ensures that the primary pseudonyms are never disclosed to third parties, not even to the participant.

## Data quality, validation and planned statistical analysis

The statistical analysis of TRUST is conducted by a team of trained statisticians, bioinformaticians, and experienced data scientists, in addition to machine learning architects at the University Medical Center Hamburg-Eppendorf and selected collaboration partners. All data stored in the data platform is monitored continuously and at milestones via pre-configured rule-based algorithms and statistical plausibility and integrity checks. Flagged or missing values is periodically reviewed against source documentation and corrected in the main database with audit-trail documentation.

All analyses of the TRUST cohort and its sub-cohorts will be defined in pre-specified analysis plans, starting with the analysis of the main outcome that includes the follow-up data collected in 2024 and 2025 and is expected in 2026. Double-checked missing data will be handled according to prespecified analysis plans using complete-case analyses, explicit missingness categories where appropriate, or imputation strategies. Multiple imputation can be applied when methodologically justified, whereas variables with non-imputable missingness will be excluded from specific models. Sensitivity analyses will be performed whenever feasible to assess the robustness of findings.

Outcomes will be evaluated using Cox proportional hazard models, incorporating clinical covariates and biomolecule concentrations. The first primary endpoint will be analyzed stratified by the main study cohort. Cumulative incidence curves will be presented using the Aalen-Johansen estimator to account for death as a competing event. Outcomes, including death, will be displayed using Kaplan-Meier curves. Sub-analyses of TRUST will be conducted in accordance with the specific clinical questions and datasets under investigation, including access to imaging and electroanatomical mapping data, analyses of digital ECGs, and analyses of the biosamples. All microservices to handle data processing within TRUST’s data platform are built in Python 3^19^ and deployed via Docker.^20^

## Statistical analysis of the current cohort profile

This paper reports baseline characteristics of the first 1500 patients. These were validated in a comprehensive data review and monitoring process in Q1 and Q2 2025. Descriptive statistics were used to describe the characteristics of the sub-cohorts. Cohort differences were compared univariately by Chi-squared tests for categorical variables and common parametric and non-parametric tests for the comparison of the central tendency. All statistical analyses in this report were performed using Python 3.12, SciPy, scikit-learn, and matplotlib for plotting.

## Results

### Patients

The first patient was enrolled in TRUST on 17 March 2021. Inclusion of new patients was paused on 17 June 2024 after enrolment of 3000 patients. Inclusion rate was stable over time (*Figure 3A*) at a median rate of 19 participants per week. To assess potential sources of selection bias, inclusion rates and reasons for non-participation were evaluated in a predefined recruitment window from January 1st until 15 March 2023. Herein, 340 patients were approached for inclusion after excluding those who did not show up to their elective appointments. Of these, 37/340 (11%) were already enrolled at prior visit, while 175/340 (51%) were newly enrolled, consented, and completed the baseline assessment. Non-participation (128/340; 38%) was occasionally due to patient refusal in 21/340 (6%), including 3/21 (14%) due to language barriers, but more often due to workflow-related constraints during pre-procedural evaluations 107/340 (31%).

**Figure 3 oeag002-F3:**
[figure not shown]
Inclusion and biobanking overview. Inclusion rate related to the number of performed electrophysiological procedures since initiation of the TRUST study on 17 March 2021 (2A), biobanking rate since initiation of TRUST (2B). The inclusion line is displayed as a rolling mean over 14 days of the daily inclusion rate (blue line), a line of cumulative inclusions (red line) as well as a rolling mean over 14 days of daily performed electrophysiological procedures. The daily biobanking rate is evenly displayed along with a red line indicating a rolling mean over 7 days.

### Biosamples

By June 2024, 3079 biosamples from 2257 participants have been collected and stored at −80°C in a standardized, central biorepository (*Figure 3B*). Biobanking at baseline is currently available from 2146 (72%) participants. Pre- and post-procedural blood sampling is available from 239 procedures in 239 participants before and after ablation. Opportunistic follow-up samples (n = 277) have been collected from 255 participants at future hospitalizations or study-related follow-up visits, with a median biobanking follow-up time of 11 [IQR: 6;13] months after inclusion.

### Baseline characteristics of the first 1500 patients

Validated and clean data from the first 1500 patients were compared by presenting arrhythmia. Most patients (1077/1500 (72%)) presented with AF or atrial tachycardias (AT). SVT or non-AF-related AT was the presenting arrhythmia in 239 (16%) patients, and VT or PVC was the main arrhythmia in 161/1500 (11%). Inherited cardiac conditions (9 patients (1%)) and AF-related cardiac surgery (14 patients 1%)) were rarer hospitalization causes at enrollment. Median age upon inclusion was 64 years [IQR: 55, 74], and 562 (37%) were women. Distribution of comorbidities varied between subgroups. The highest age and comorbidity burden was observed in the heart surgery and the AF/AT sub-cohorts (*Table 4*). A history of coronary artery disease, coronary intervention, or myocardial infarction was most common in patients with VT/PVC. Coronary artery disease was present in 51/161 (32%) of VT/PVC participants and 286/1077 (27%) of the AT/AF participants (p_AF/AT-vs-VT/PVC_ < 0.001). Prior coronary intervention was reported in 52/161 (33%) of VT/PVC participants 190/1077 (18%) of the AF/AT participants (p_AF/AT-vs-VT/PVC_ < 0.001), while history of myocardial infarction was present in 24/161 (15%) of VT/PVC participants and 84/1077 (8%) of AF/AT participants (p_AF/AT-vs-VT/PVC_ < 0.001, *Table 4*). Most patients (91%) underwent ablation or electrophysiological testing within 1 month after enrolment (*Figure 4*, *Table 5*).

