40–49%, N (%)	153 (10)	118 (11)	18 (11)	15 (6)		2 (14)
30–39%, N (%)	109 (7.0)	86 (8.0)	19 (12)	4 (1.7)		
<30%, N (%)	77 (5.0)	51 (4.7)	19 (12)	6 (2.5)		1 (7)
Diastolic septal wall width, mm	11.0 (3.2)	11.3 (2.8)	10.1 (1.8)	10.4 (4.8)	8.7(1.5)	11.8 (1.6)
Right ventricular pressure, systolic, mmHg	25 [20,32]	26 [22,33]	22 [18,27]	22 [18,29]	18 [18,18]	28 [21,45]
Left atrial volume, indexed, mL/m^2^	33 [24,42]	35 [27,44]	30 [23,39]	24 [19,29]	18 [17,22]	49 [42,58]
Present Heart Disease						
Heart failure, N (%)	894 (60)	725 (67)	90 (56)	67 (28)		12 (86)
HFpEF, N (%)	548 (37)	466 (43)	30 (19)	43 (18)		9 (64)
HFmrEF, N (%)	158 (11)	122 (11)	20 (12)	14 (6)		2 (14)
HFrEF, N (%)	188 (13)	137 (9)	40 (25)	10 (4.1)		1 (7)
Coronary artery disease, N (%)	369 (25)	286 (26)	51 (32)	23 (10)		9 (64)
Prior myocardial infarction, N (%)	117 (8)	84 (8)	24 (15)	9 (3.8)		
Valvular heart disease, N (%)	326 (22)	256 (24)	39 (24)	20 (8)		11 (79)
Medical History						
Arterial hypertension, N (%)	921 (61)	751 (70)	72 (44)	87 (36)	1 (11)	10 (71)
Diabetes mellitus, N (%)	168 (11)	125 (12)	18 (11)	20 (8)		5 (36)
Hypercholesterinemia, N (%)	560 (37)	449 (42)	61 (38)	41 (17)		9 (64)
Peripheral artery disease, N (%)	42 (2.8)	37 (3.4)	3 (1.9)	1 (0.4)		1 (7)
Pulmonary embolism, N (%)	43 (2.8)	33 (3.1)	2 (1.3)	8 (3.3)		
Chronic obstructive pulmonary disease, N (%)	55 (3.6)	47 (2.4)	5 (3.1)	2 (0.8)		1 (7)
Obstructive sleep apnea syndrome, N (%)	106 (7)	92 (9)	8 (5)	6 (2.5)		
Estimated glomerular filtration rate (CKD-EPI), mL/min/1.73 m^2^	72 (22)	71 (20)	79 (23)	92 (20)	93 (17)	53 (24)
Prior major bleeding (ISTH), N (%)	31 (2.0)	29 (2.7)	1 (0.6)	1 (0.4)		
Prior stroke or TIA, N (%)	112 (8)	93 (9)	10 (6)	7 (2.9)		2 (14)
Any malignant disease, N (%)	191 (13)	155 (14)	18 (11)	16 (7)		2 (14)
Rheumatological disease, N (%)	50 (3.3)	38 (3.5)	5 (3.1)	6 (2.5)		1 (7)
Hyperthyroidism, N (%)	59 (3.9)	47 (4.3)	8 (5)	4 (1.7)		
Hypothyroidism, N (%)	71 (4.7)	39 (3.6)	14 (9)	18 (8)		

Data is displayed stratified by the chief-complaint cohort assigned at inclusion into the TRUST registry.

AF, Atrial fibrillation; HF, Heart failure; HFmrEF, Heart failure with mildly reduced ejection fraction; HFpEF, Heart failure with preserved ejection fraction; HFrEF, Heart failure with reduced ejection fraction; ICC, Inherited cardiac condition; ISTH, International Society of Thrombosis and Hemostasis; SVT, Supraventricular tachycardia; VT, Ventricular tachycardia.

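### Two of the three pairwise p-values given as < 0.001 do not follow from their counts: coronary artery disease gives p = 0.17 and myocardial infarction p = 0.003

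*Protocol article*

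**What the plan says.** The section of the protocol article on the statistical analysis of the current cohort profile names the test: "Cohort differences were compared univariately by Chi-squared tests for categorical variables". It mentions no multiplicity adjustment.

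Under Baseline characteristics of the first 1500 patients, the Results compare the AF/AT and VT/PVC cohorts on three items. Each p-value carries a subscript naming that pair:

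- Coronary artery disease: "Coronary artery disease was present in 51/161 (32%) of VT/PVC participants and 286/1077 (27%) of the AT/AF participants (p_AF/AT-vs-VT/PVC_ < 0.001".
- Prior coronary intervention: "Prior coronary intervention was reported in 52/161 (33%) of VT/PVC participants 190/1077 (18%) of the AF/AT participants (p_AF/AT-vs-VT/PVC_ < 0.001".
- Prior myocardial infarction: "history of myocardial infarction was present in 24/161 (15%) of VT/PVC participants and 84/1077 (8%) of AF/AT participants (p_AF/AT-vs-VT/PVC_ < 0.001".

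The sentence that introduces them says that a history of coronary artery disease, "coronary intervention, or myocardial infarction was most common in patients with VT/PVC".

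Table 4 repeats two of the three sets of counts: "Coronary artery disease, N (%) 369 (25) 286 (26) 51 (32) 23 (10" and "Prior myocardial infarction, N (%) 117 (8) 84 (8) 24 (15) 9 (3.8". It has no row for coronary intervention.

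**The concern.** Proportions of 32% and 27%, with only 161 patients in the smaller group, should not give p < 0.001. Both denominators and both numerators are printed and the test is named, so the value can be checked directly.

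As printed, a reader takes a 5-point difference as overwhelming evidence that coronary artery disease is more frequent in the ventricular arrhythmia cohort than in the AF/AT cohort. The wording on which cohort has the highest frequency adds to that impression, although Table 4 shows a higher share of coronary artery disease in the Surgery cohort. Three identical bounds, only one of which looks plausible at a glance, also raise the question of which test was actually printed.

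**Working it through.** **Inputs.** The counts come from the Results text. Table 4 confirms them for coronary artery disease (CAD) and myocardial infarction (MI).

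| Item | VT/PVC | AF/AT | Stated p |
|---|---|---|---|
| CAD | 51/161 (31.7%) | 286/1077 (26.6%) | < 0.001 |
| Coronary intervention | 52/161 (32.3%) | 190/1077 (17.6%) | < 0.001 |
| MI | 24/161 (14.9%) | 84/1077 (7.8%) | < 0.001 |

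**Formula.** For a two-by-two table with cells a, b (VT/PVC with, without) and c, d (AF/AT with, without), Pearson's statistic is N(ad − bc)² / (product of the four margins), on 1 degree of freedom, with N = 161 + 1077 = 1238.

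**Coronary intervention (the value that reproduces).** ad − bc = 52×887 − 109×190 = 25,414. Statistic = 1238 × 25,414² / (161 × 1077 × 242 × 996) = 19.13, p = 0.000012. This agrees with the article.

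**CAD.** ad − bc = 51×791 − 110×286 = 8,881. Statistic = 1238 × 8,881² / (161 × 1077 × 337 × 901) = 1.85, p = 0.173.

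**MI.** ad − bc = 24×993 − 137×84 = 12,324. Statistic = 1238 × 12,324² / (161 × 1077 × 108 × 1130) = 8.89, p = 0.0029.

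**Other choices of test on the same counts.**

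| Test | CAD | MI |
|---|---|---|
| Pearson | 0.173 | 0.0029 |
| Continuity-corrected | 0.205 | 0.0046 |
| Likelihood ratio | 0.179 | 0.0055 |
| Fisher, two-sided | 0.184 | 0.0063 |
| Wald, unpooled | 0.190 | 0.015 |
| Smallest one-sided | 0.087 | 0.0014 |

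None reaches 0.001 for either item. The Wald interval for the CAD difference is 5.1 points (95% CI -2.5 to 12.8).

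**Distance from the stated bound.** With AF/AT held at 286/1077, VT/PVC would need 63/161 (39%) for the uncorrected test to fall below 0.001, against 51 observed.

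**Missing data.** Denominators of 155, 158 and 161 for VT/PVC were crossed with 988, 1030 and 1077 for AF/AT. The smallest uncorrected p is 0.097 for CAD and 0.0016 for MI. MI falls below 0.001 (p = 0.0008) only if 155 is paired with 1119, which is more patients than the AF/AT cohort contains.

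**A possible source.** The blank cells in Table 4 can be read as zero, because the filled cells add up to the totals: 286 + 51 + 23 + 9 = 369 for CAD and 84 + 24 + 9 = 117 for MI. The chi-squared test across all five cohorts then gives p = 3.1×10⁻¹⁰ for CAD and p = 0.0009 for MI. Both are below 0.001. This fits an all-cohort p-value printed under a pairwise label, but the article does not say so.

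**Which cohort is highest.** CAD: Surgery 9/14 = 64%, VT/PVC 51/161 = 32%. MI: VT/PVC is highest in Table 4. Coronary intervention cannot be checked beyond the two cohorts in the text.

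**Smaller inconsistencies.** In VT/PVC, prior coronary intervention (52) exceeds CAD (51). The fraction 286/1077 = 26.6% is printed as 27% in the text and 26 in Table 4, and 52/161 = 32.3% is printed as 33%.

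**The case against.** The strongest reply concerns weight, not arithmetic. These are univariate descriptive comparisons in a cohort that the article says was not built around one hypothesis. No outcome, planned analysis or stated objective uses these p-values, and neither the Abstract nor the Conclusion cites the contrast. The Discussion's remarks on ischaemic disease concern the 35 patients with VT ablation and rest on separate counts. All of that stands and limits the consequence, but it does not make the printed values right.

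Two of the three ischaemic contrasts also remain statistically significant at 0.05, so the general direction of the paragraph survives. That is correct, and MI should carry less weight than CAD: only its bound is wrong.

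Suspicion of other p-values should be kept in proportion. The remaining pairwise p-value in the text, on reduced ejection fraction in VT ablation patients, does reproduce: 17/33 gives p = 2×10⁻¹⁰ against 137/1077, or 5×10⁻⁶ against 137/725. The visible error is confined to two values.

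The counts rather than the p-values could be at fault, and the document alone cannot exclude that. However, text and Table 4 agree on the CAD and MI counts, and the article describes the data as validated. The excess of interventions over CAD cases is a query about definitions, not proof of miscoding. The threshold of 63 applies to the uncorrected test; with the continuity correction it is 64.

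On the highest-frequency claim, the Surgery cohort has only 14 patients, and the article does name heart surgery among the cohorts with the greatest comorbidity burden. The sentence is still wrong for CAD as written.

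**Conclusion.** The concern holds. On the printed counts and with the named test, the CAD comparison between AF/AT and VT/PVC gives p = 0.17 (0.17 to 0.21 across Pearson, corrected and Fisher tests), not < 0.001, and the stated difference is not supported. The MI comparison gives p = 0.003 (0.003 to 0.006 across the same tests): the difference is supported, the bound is not. The coronary intervention value is correct. VT/PVC does not have the highest CAD share; Surgery does.

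This rests on the printed counts and denominators being right. That all-cohort p-values were mislabelled is a plausible explanation only. The error must be corrected because a reported between-cohort difference is contradicted by its own numbers. Its reach is the baseline description; the planned main outcome analysis is unaffected.

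**What to change.** - Re-run the three AF/AT against VT/PVC comparisons as two-by-two tests from the source data. If the counts stand, print p = 0.17 for CAD and p = 0.003 for MI, and keep < 0.001 for coronary intervention.
- If all-cohort tests were intended, label them as such and remove the pairwise subscript.
- Withdraw the statement of a CAD difference between AF/AT and VT/PVC. Limit the highest-frequency claim to what Table 4 shows, noting 9/14 (64%) CAD in the Surgery cohort.
- Check the definitions and coding of CAD against prior coronary intervention in VT/PVC (51 against 52), and align the rounded percentages between text and Table 4.
- Confirm that every other pairwise p-value comes from the pair it names.

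The cost is a few short tests and edits to one paragraph. One reported contrast becomes weaker; no new data are needed.

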**Figure 4 oeag002-F4:**
[figure not shown]
Procedures performed within 1 month after inclusion. Patients enrolled into the registry were assigned to chief-complaint cohorts (Atrial fibrillation or AF-related atrial tachycardia (AF/AT, blue), non-AF-related supraventricular tachycardia (SVT, red), Premature ventricular complexes or ventricular tachycardia (PVC/VT, orange), Inherited cardiac conditions and Heart surgery—subsumed in one category (‘Other’, green)). The sunburst plot shows cohort assignments upon inclusion in the inner circle and interventional procedures performed within 1 month after inclusion in the outer circle. Procedure categories with less than 20 patients were subsumed (‘Other’). Blank spaces in the outer circle indicate the share of patients without an interventional procedure performed within 1 month after inclusion. AF, Atrial fibrillation; AT, Atrial tachycardia; CTI, cavotricuspid isthmus; PVC, premature ventricular complexes; (i)PVI, (index) pulmonary vein isolation; SVT, supraventricular tachycardia; VT, ventricular tachycardia.

**Table 4 oeag002-T4:** Baseline characteristics, comorbidities and echocardiography measurements of the first 1500 patients included in TRUST between March, 2021, and March, 2022

	Overall	AF and AT	VT and PVC	Non-AF SVTs	ICC	Surgery
N participants (%)	1500 (100)	1077 (72)	161 (11)	239 (16)	9 (1)	14 (1)
Age, N (%)	64 [55,74]	67 [58,75]	58 [47,70]	52 [35,65]	33 [27,59]	66 [60,77]
Female sex, N (%)	562 (37)	385 (36)	56 (34)	111 (46)	8 (88)	2 (14)
Body mass index (kg/m^2^)	27 [24,30]	27 [24,31]	26 [23,30]	26 [23,30]	24 [21,27]	26 [23,28]
CHA_2_DS_2_-VA Score, median and mean	2 [1,4] 3 (2)	3 [2,4] 2 (2)	2 [1,3] 2 (2)	1 [0,2] 1 (1)	0 [0,0] 0 (0)	4 [2,5] 4 (2)
CHA_2_DS_2_-VA Score ≥ 2, N (%)	1022 (68)	845 (78)	80 (50)	85 (36)		12 (86)
Heart rhythm						
Atrial fibrillation, N (%)	1121 (75)	1077 (100)	34 (21)	0 (0)	0 (0)	10 (71)
Paroxysmal atrial fibrillation, N (%)	446 (30)	424 (40)	16 (10)	0 (0)		6 (43)
Months since first diagnosis, N (%)	12 [4,41]	12 [4,41]	24 [14,51]			6 [6,6]
Atrial flutter, N (%)	296 (20)	235 (22)	1 (0.6)	59 (25)		1 (7)
Prior left atrial tachycardia, N (%)	111 (7)	107 (7)	3 (1.9)	1 (0.4)		
Prior sustained ventricular tachycardia, N (%)	86 (6)	20 (1.8)	58 (36)	5 (2.1)	1 (11)	2 (14)
Prior catheter ablation, N (%)	517 (34)	435 (29)	43 (26)	38 (16)		1 (7)
Echocardiography						
Left ventricular ejection fraction, N (%)						
≥50%, N (%)	1086 (72)	786 (73)	88 (54)	196 (82)	9 (100)	10 (71)
40–49%, N (%)	153 (10)	118 (11)	18 (11)	15 (6)		2 (14)
30–39%, N (%)	109 (7.0)	86 (8.0)	19 (12)	4 (1.7)		
<30%, N (%)	77 (5.0)	51 (4.7)	19 (12)	6 (2.5)		1 (7)
Diastolic septal wall width, mm	11.0 (3.2)	11.3 (2.8)	10.1 (1.8)	10.4 (4.8)	8.7(1.5)	11.8 (1.6)
Right ventricular pressure, systolic, mmHg	25 [20,32]	26 [22,33]	22 [18,27]	22 [18,29]	18 [18,18]	28 [21,45]
Left atrial volume, indexed, mL/m^2^	33 [24,42]	35 [27,44]	30 [23,39]	24 [19,29]	18 [17,22]	49 [42,58]
Present Heart Disease						
Heart failure, N (%)	894 (60)	725 (67)	90 (56)	67 (28)		12 (86)
HFpEF, N (%)	548 (37)	466 (43)	30 (19)	43 (18)		9 (64)
HFmrEF, N (%)	158 (11)	122 (11)	20 (12)	14 (6)		2 (14)
HFrEF, N (%)	188 (13)	137 (9)	40 (25)	10 (4.1)		1 (7)
Coronary artery disease, N (%)	369 (25)	286 (26)	51 (32)	23 (10)		9 (64)
Prior myocardial infarction, N (%)	117 (8)	84 (8)	24 (15)	9 (3.8)		
Valvular heart disease, N (%)	326 (22)	256 (24)	39 (24)	20 (8)		11 (79)
Medical History						
Arterial hypertension, N (%)	921 (61)	751 (70)	72 (44)	87 (36)	1 (11)	10 (71)
Diabetes mellitus, N (%)	168 (11)	125 (12)	18 (11)	20 (8)		5 (36)
Hypercholesterinemia, N (%)	560 (37)	449 (42)	61 (38)	41 (17)		9 (64)
Peripheral artery disease, N (%)	42 (2.8)	37 (3.4)	3 (1.9)	1 (0.4)		1 (7)
Pulmonary embolism, N (%)	43 (2.8)	33 (3.1)	2 (1.3)	8 (3.3)		
Chronic obstructive pulmonary disease, N (%)	55 (3.6)	47 (2.4)	5 (3.1)	2 (0.8)		1 (7)
Obstructive sleep apnea syndrome, N (%)	106 (7)	92 (9)	8 (5)	6 (2.5)		
Estimated glomerular filtration rate (CKD-EPI), mL/min/1.73 m^2^	72 (22)	71 (20)	79 (23)	92 (20)	93 (17)	53 (24)
Prior major bleeding (ISTH), N (%)	31 (2.0)	29 (2.7)	1 (0.6)	1 (0.4)		
Prior stroke or TIA, N (%)	112 (8)	93 (9)	10 (6)	7 (2.9)		2 (14)
Any malignant disease, N (%)	191 (13)	155 (14)	18 (11)	16 (7)		2 (14)
Rheumatological disease, N (%)	50 (3.3)	38 (3.5)	5 (3.1)	6 (2.5)		1 (7)
Hyperthyroidism, N (%)	59 (3.9)	47 (4.3)	8 (5)	4 (1.7)		
Hypothyroidism, N (%)	71 (4.7)	39 (3.6)	14 (9)	18 (8)		

Data is displayed stratified by the chief-complaint cohort assigned at inclusion into the TRUST registry.

AF, Atrial fibrillation; HF, Heart failure; HFmrEF, Heart failure with mildly reduced ejection fraction; HFpEF, Heart failure with preserved ejection fraction; HFrEF, Heart failure with reduced ejection fraction; ICC, Inherited cardiac condition; ISTH, International Society of Thrombosis and Hemostasis; SVT, Supraventricular tachycardia; VT, Ventricular tachycardia.

**Table 5 oeag002-T5:** Electrophysiological procedures performed within one month after inclusion in the atrial fibrillation (AF) or AF-related atrial tachycardia (AT) chief-complain cohort, the ventricular arrhythmias cohort (PVC/VT), and the non-AF-related supraventricular tachycardia cohort (SVT) in TRUST

	AF and AT	VT and PVC	Non-AF SVTs
**N patients in cohort (%)**	1077 (72)	161 (11)	239 (16)
**N patients with an interventional procedure performed within one month after inclusion**	990/1077 (92)	146/161 (91)	227/239 (95)
First pulmonary vein isolation	584/990 (59)		
Repeat pulmonary vein isolation Repeat atrial fibrillation ablation Focal or macro-reentry atrial tachycardia ablation (left and right)	345/990 (35)		28/227 (12)
Typical atrial flutter ablation	25/990 (3)		44/227 (19)
Ablation of other SVT	14/990 (1)		155/227 (68)
PVC ablation		100/146 (68)	
VT ablation		35/146 (24)	
Programmed stimulation without ablation		5/146 (3)	
Left atrial appendage occlusion	20/990 (2)		
Other procedures	2/990 (0)	6/146 (4)	
**No procedure performed within one month after inclusion**	87/1077 (8)	15/161 (9)	13/239 (5)

AF, Atrial fibrillation; AT, Atrial tachycardia; CTI, Cavotricuspid isthmus; LAA, Left atrial appendage; PVC, Premature ventricular complexes; SVT, Supraventricular tachycardia; VT, Ventricular tachycardia.

